#### **10.4 Subgroup Analysis**

Not applicable.

#### **10.5 Interim Analysis**

No interim analysis is planned in this study.

#### **10.6 Multiplicity**

Not applicable.

#### **10.7 Handling of Missing Data**

In FAS immunogenicity analysis, LOCF (Last Observation Carried Forward) method will be used to impute the missing values in antibody data after vaccination. And other immunogenicity endpoints will be derived from the imputed data. The missing data in safety and immunogenicity persistence evaluation will be not imputed.

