**Immunogenicity Observation:**

Blood samples of all the participants will be collected before the vaccination of booster dose and 14 days, 28 days, 3 months, 6 months, 9 months and 12 months after booster vaccination for detection of neutralizing antibodies. The neutralizing antibody will be tested by a micro-dose cytopathogenic effect (CPE) assay.

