| Neutralizing Antibody/IgG Test                                          | ✓                                                                                       |                                                                                         |                                                                                         | ✓                                                                                        |                                                                                            | ✓                                                                                          |                                                                                                    | ✓                                                                                                  |                                                                                                    |                                                                                                    | ✓                                                                                                  | ✓                                                                                                  | ✓                                                                                                   |

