**CONFIDENTIAL**

## 10. STATISTICAL CONSIDERATIONS

### 10.1 Sample Size Considerations

#### Primary indicators:

- The antibody GMT (Omicron) in the experimental group was superior to that in the control group 14 days after immunization.
- H0:  $\delta \leq 0.0212$  vs. H1:  $\delta > 0.0212$  (both are logarithmic scale, equivalent to GMT ratio 95%CI > 1.05)

**Calculating basis for sample size:** by referring to the relevant data of this product in ex-China clinical trials, 0.55 (logarithmic scale) is taken as the standard difference in antibody titer of recombinant COVID-19 vaccine (CHO cell). The probability of type I error  $\alpha=0.025$  (one-sided); power  $1-\beta=0.9$ ; superiority margin  $\Delta=0.0212$  (logarithmic scale, i.e. GMT test group/GMT control group  $\geq 1.05$ ); the test group and the control group are designed according to 1:1.

| Test level
(one sided) | Target     | N of each
group | Superiority
margin         | Actual level
of
difference
between
test group
and control
group | SD          | Total N
after
considering
20% drop-
out |
|---------------------------|------------|--------------------|-------------------------------|-----------------------------------------------------------------------------------|-------------|-----------------------------------------------------|
| 0.025              | 0.9 | 166         | 0.0212
(1.05 fold) | 0.200(
1.6 fold)                                                       | 0.55 | 398                                          |
| 0.025                     | 0.8        | 139                | 0.1139
(1.3)               | 0.30
(2 fold)                                                                  | 0.55        | 348                                                 |
| 0.025                     | 0.85       | 158                | 0.1139
(1.3)               | 0.30                                                                              | 0.55        | 396                                                 |
| 0.025                     | 0.9        | 185                | 0.1139
(1.3)               | 0.30                                                                              | 0.55        | 462                                                 |

CONFIDENTIAL

|       |      |     |                |      |      |      |
|-------|------|-----|----------------|------|------|------|

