**Secondary indicators:**

The antibody GMT (prototype strain) of the experimental group was not inferior to that of the control group 14 days after immunization.

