## 10.2 Analysis Set

**Full Analysis Set (FAS):** It includes all randomized participants who follow ITT principle, receive 1 dose of vaccine, and have valid immunogenicity data before the first dose.

**Per-Protocol Set (PPS):** It includes all participants who do not violate the inclusion criteria/exclusion criteria, receive 1 dose of vaccine, and have both valid pre- and post-vaccination immunogenicity data. PPS will be defined for immunogenicity evaluations 14 and 28 days after booster vaccination, respectively.

**Immunogenicity Persistence Set (IPS):** It includes the participants who are collected with blood samples at each time point for immunogenicity persistence evaluation and with valid

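### In the full analysis set, LOCF replaces a missing day-14 titre with the pre-booster titre, which biases the GMT ratio, costs superiority power and inflates the non-inferiority type I error

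*Protocol*

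**What the plan says.** Section 10.7 states that, in the FAS immunogenicity analysis, "LOCF (Last Observation Carried Forward) method will be used to impute the missing values in antibody data after vaccination". It continues: "And other immunogenicity endpoints will be derived from the imputed data". Section 10.2 admits to the FAS randomized participants who "receive 1 dose of vaccine, and have valid immunogenicity data before the first dose"; no post-booster titre is required. The per-protocol set (PPS), by contrast, takes participants who "have both valid pre- and post-vaccination immunogenicity data".

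Section 4.2 has blood drawn "before the vaccination of booster dose and 14 days, 28 days, 3 months, 6 months, 9 months and 12 months after booster vaccination". In the Schedule of Events, the row "Neutralizing Antibody/IgG Test" is marked at V1 (day 0) and next at V4 (day 14), with nothing at V2 or V3.

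Day 14 carries both sizing hypotheses in Section 10.1. The Omicron GMT in the experimental group is to be shown to be one that "was superior to that in the control group 14 days after immunization". The prototype-strain GMT, listed as a secondary indicator, is to be shown to be one that "was not inferior to that of the control group 14 days after immunization". Section 4.4 states both the superiority and the non-inferiority hypothesis for Omicron.

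**The concern.** For a participant without a day-14 serum, the last observation is the titre from before the booster. LOCF then gives that participant a fold rise of exactly 1, a failure on the 4-fold rise rate, and an ANCOVA response equal to its own covariate. That is not a plausible day-14 titre for someone who was vaccinated.

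LOCF is often defended as conservative. That defence fails here for non-inferiority, because shrinking the ratio toward 1 moves a truly inferior product toward the acceptance region. For superiority the same shrinkage wastes power. If the arms lose different shares of samples, the rule creates a difference that does not exist.

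**Working it through.** **Inputs from the protocol (Sections 10.1 and 10.3.3).** One-sided alpha 0.025; power 0.90; SD 0.55 log10; non-inferiority margin −0.17609 (ratio 2/3) with true difference 0; superiority margin 0.0212 with true difference 0.200 (ratio 10^0.200 = 1.585); 1:1 allocation; 20% drop-out; 516 enrolled; ANCOVA with log baseline titre as covariate.

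**Assumptions, not in the protocol.** Mean rise after boosting in the control arm, 0 to 1.5 log10; baseline SD equal to 0.55 in the approximation; missingness unrelated to titre.

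**The plan's own figure.** n = 2(1.960 + 1.2816)² × 0.55² / 0.17609² = 205.01, so 206 per group. 206/0.8 = 257.5, so 258 per group and 516 in total. This reproduces. (The superiority row does not: the same formula with 0.200 − 0.0212 gives 199 per group, not 166. That is a separate matter; 516 is set by the non-inferiority row.)

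**Effect of LOCF, equal missing share d.**
- Expected difference: (1 − d) × true difference.
- Variance in each arm: 0.55² + d(1 − d) × (mean rise in that arm)².
- 258 per arm, since every FAS member receives a value.

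*Worked case: d = 0.20, control rise 1.0.*
- Superiority: expected difference 0.8 × 0.200 = 0.160, ratio 1.445. Variances 0.3025 + 0.16 × 1.0² = 0.4625 and 0.3025 + 0.16 × 1.2² = 0.5329. SE = √(0.9954/258) = 0.0621. z = (0.160 − 0.0212)/0.0621 − 1.96 = 0.27, power 0.61.
- Observed cases, 206 per group: SE = 0.55√(2/206) = 0.0542. z = 0.1788/0.0542 − 1.96 = 1.34, power 0.91.
- Non-inferiority at a true ratio of 2/3: expected difference 0.8 × (−0.17609) = −0.1409, ratio 0.723. Variances 0.4625 and 0.3025 + 0.16 × 0.824² = 0.4111, SE = 0.0582. z = 0.0352/0.0582 − 1.96 = −1.35, type I error 0.088 against 0.025.

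| Missing at day 14 | 1.585 appears as | Superiority power, observed cases | Superiority power, LOCF | 2/3 appears as | Non-inferiority type I error, LOCF |
|---|---|---|---|---|---|
| 2% | 1.570 | 0.955 | 0.917–0.950 | 0.672 | 0.029–0.030 |
| 5% | 1.549 | 0.949 | 0.837–0.936 | 0.680 | 0.036–0.038 |
| 10% | 1.514 | 0.939 | 0.695–0.905 | 0.694 | 0.047–0.055 |
| 20% | 1.445 | 0.910 | 0.463–0.814 | 0.723 | 0.073–0.108 |

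In each range the lower value belongs to a control rise of 1.5 log10 and the higher to a rise of 0.

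**Simulated ANCOVA with baseline covariate.**
- Baseline/day-14 correlation 0.3 and 0.6, rise 0.5 to 1.5: at 20% missing, superiority power is 0.47–0.91 with LOCF against 0.92–0.98 with observed cases, and non-inferiority type I error is 0.076–0.148 against 0.023–0.026.
- Correlation 0.4, baseline SD 0.45, rise 0.6 / 0.9 / 1.2: at 20% missing, power is 0.826 / 0.727 / 0.626 against about 0.95. Type I error is 0.114 / 0.100 / 0.089 at 20% missing, 0.055 / 0.046 / 0.049 at 10% and about 0.04 at 5%.

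**Unequal missingness.** With control share d_c, test share d_t and control rise r, the expected difference is (1 − d_t) × true difference + r(d_c − d_t). With a true difference of 0, a 5-point gap (10% versus 15%) gives 0.05 × 0.6 = 0.03 to 0.05 × 1.2 = 0.06 log10 of pure artefact. Simulated with r = 1.0 and correlation 0.3:
- control 10%, test 5% missing: non-inferiority type I error 0.21;
- control 5%, test 10% missing: type I error 0.004, and the 1.585 ratio appears as 1.35.

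**The case against.** The mechanism is not in dispute; the objections concern reach and size.

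- **Only the FAS is affected.** The PPS requires both titres and is never imputed. This is true, but the protocol does not say which set carries the immunogenicity conclusions, so the PPS cannot be relied on to neutralise the problem.
- **20% is not a day-14 figure.** It is a general drop-out allowance in a trial with 12 months of follow-up, and day 14 is the first draw after a single dose. This stands. At 2% missing the damage is small, and at 5% the type I error is about 0.04. The 20% row is the severe end, although it is the only loss figure the protocol gives.
- **The Omicron superiority test is not made anti-conservative when missingness is equal.** Correct: simulated superiority type I error stayed at about 0.017–0.030. There the cost is power and a biased estimate. The inflation concerns the non-inferiority claim.
- **Shrinkage toward 1 needs similar missingness in both arms.** Correct. Otherwise the bias can go either way, which makes the rule no safer.
- **The simulated power with observed cases includes an assumed covariate gain, and the simulated model omits the vaccination-time effect of Section 10.3.3.** Fair. The unadjusted comparator is 0.91, and the loss against it remains.
- **A missing day-28 titre would take the day-14 value.** It would if that value exists. A participant missing both still receives the pre-booster titre.

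One might read Section 10.7 as carrying forward post-dose values only. The text does not say so, and on that reading the rule could never fill a day-14 value.

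**Conclusion.** The concern holds. Sections 4.2, 10.2 and 10.7 together mean that every missing day-14 titre in the FAS is replaced by the pre-booster titre, and nothing elsewhere in the protocol corrects this. With equal missingness the log difference is multiplied by (1 − d). At 10% missing, the non-inferiority type I error is about twice nominal and superiority power drops from 0.94 to 0.70–0.91. At 20%, the type I error is three to four times nominal in the approximation and power is 0.46–0.81 against 0.91. These sizes rest on the assumed mean rise, baseline variance and correlation, on missingness unrelated to titre, and on the FAS carrying the claim. The direction under equal missingness does not depend on the assumed values. This is a method the protocol itself fixes, not a detail left to a later plan, and it should be changed before unblinding so that the choice of method cannot follow the results.

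**What to change.** Reword Section 10.7:

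- Remove LOCF for days 14 and 28, and state that a pre-booster titre is never carried forward.
- Analyse FAS log10 titres with a repeated-measures likelihood model on days 14 and 28 with baseline as covariate, or by multiple imputation within arm under a missing-at-random assumption.
- Derive the 4-fold rise rate from the same multiple imputations. If the likelihood model is used for the GMT, imputation is still needed for this endpoint.
- Keep imputation of no response only as a labelled sensitivity analysis.
- Name the primary set for immunogenicity, and use the PPS as well as the FAS for the non-inferiority claim.

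The cost is a wording change in Section 10.7, a matching sentence on the analysis sets, and slightly more programming. No extra participants, samples or visits are needed.

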**CONFIDENTIAL**

## 11. ETHICAL AND REGULATORY MATTERS

This clinical trial will be conducted by the Sponsor, the Investigator, and delegated Investigator staff and Sub-investigator, in accordance with consensus ethics principles derived from international ethics guidelines, including the Declaration of Helsinki, and the ICH guidelines for Good Clinical Practice (GCP), all applicable laws, rules and regulations.

### 11.1. Ethics Committees and Regulatory Authorities

The ICH-GCP (E6 (R2)) guidelines require that approval must be obtained from an Independent Ethics Committee (IEC) prior to participation of human participants in research studies. Prior to the study onset, the protocol, informed consent, advertisements to be used for participant recruitment, and any other written information regarding this study to be provided to the participant or the participant's legal guardian must be approved by the IEC. Documentation of the relevant national IEC approval and of the IEC compliance with ICH Guideline E6 will be maintained by the site and will be available for review by the Sponsor or its designee or by the authorized members of regulatory agencies.

The respective Ethics Committees approvals should be signed by the IEC Chairman or designee and must identify the IEC name and address, the clinical protocol by title and/or protocol number and the date approval and/or favorable opinion was granted. Also, a list of the EC members who attended the meeting when the Protocol/ Protocol amendment was discussed, including names and qualifications, needs to be provided by the EC to the investigator or the Sponsor/ his representative.

If any alterations, other than changes of administrative nature only, are made to the study protocol, a formal protocol amendment will be issued and submitted to relevant IEC for approval. The amendment will not be implemented until IEC approval, except in cases where immediate implementation is necessary to eliminate or prevent imminent hazard to the participants.

In the same way, approval from regulatory authorities (RA) should be granted before beginning the study. The investigator or the Sponsor representative must provide to the

**CONFIDENTIAL**

regulatory authorities the name and address of the EC along with a statement from the EC that it is organized according to GCP and the applicable laws and regulations. Amendments will be submitted to RA too for approval.

### **11.2. Responsibilities of the Sponsor**

The Sponsor of this clinical trial is responsible to regulatory authorities for taking all reasonable steps to ensure the proper conduct of the clinical trial as regards ethics, clinical trial protocol compliance, and integrity and validity of the data recorded on the e-CRFs. Thus, the main duty of the monitoring team is to help the Investigator and the Sponsor maintain a high level of ethical, scientific, technical and regulatory quality in all aspects of the clinical trial.

At regular intervals during the clinical trial, the site will be contacted, through monitoring visits, letters or telephone calls, by a representative of the monitoring team to review study progress, Investigator and participant compliance with clinical trial protocol requirements and any emergent problems. These monitoring visits will include but not be limited to review of the following aspects: participant informed consent, participant recruitment and follow-up, SAE documentation and reporting, AE documentation, IP allocation, participant compliance with the instructions, IP accountability, concomitant therapy use, and quality of data.

### **11.3. Responsibilities of the Investigator**

The Investigator is responsible for ensuring that the clinical study is performed in accordance with the protocol, the ethical principles that have their origin in the Declaration of Helsinki (version dated October 2013) as well as with the ICH Note for Guidance on Good Clinical Practice (ICH, E6, R2, 2016), relevant site SOPs and applicable regulatory requirements. These documents state that the informed consent of participants is an essential precondition for participation in the clinical study.

The Investigator is required to ensure compliance with all procedures required by the clinical trial protocol and with all study procedures provided by the Sponsor (including

**CONFIDENTIAL**

security rules). The Investigator agrees to provide reliable data and all information requested by the clinical trial protocol (with the help of the e-CRF, Discrepancy Resolution Form [DRF] or other appropriate instrument) in an accurate and legible manner according to the instructions provided and to ensure direct access to source documents by Sponsor representatives.

If any circuit includes transfer of data particular attention should be paid to the confidentiality of the participant's data to be transferred.

The Investigator may appoint such other individuals as he/she may deem appropriate as Sub-investigators to assist in the conduct of the clinical trial in accordance with the clinical trial protocol. All Sub-investigators shall be appointed and listed in a timely manner. The Sub-investigators will be supervised by and work under the responsibility of the Investigator. The Investigator will provide them with a copy of the clinical trial protocol and all necessary information.

In 1998, the US Food and Drug Administration (FDA) introduced a regulation (21 CFR, Part 54) entitled “Financial Disclosure by Clinical Investigators.” For studies conducted in any country that could result in a product submission to the FDA for marketing approval and which contribute significantly to the demonstration of efficacy and safety of the drug (named “covered studies” by the FDA), the Investigator and all sub-Investigators are obliged to disclose their financial interest which they or their spouses and dependent children may have in the Sponsor. This information is required during the study and until 12 months after its completion.

#### **11.4. Participant Information and Informed Consent**

A prerequisite for a participant participating in the study is his/her or their legal representative or parent's/guardian's written informed consent. Adequate information must therefore be given to the participant by the Investigator/designated personnel before informed consent is obtained. One or more Informed Consent Forms in the local language

**CONFIDENTIAL**

and prepared in accordance with the Note for Guidance on Good Clinical Practice (ICH, Topic E6 (R2)) will be provided by the Sponsor for the purpose of obtaining informed consent. In addition to this written information, the Investigator or his designate will inform the participant verbally. In doing so, the wording used will be chosen so that the information can be fully and readily understood by laypersons. The Informed Consent Form will be revised whenever important new information becomes available that may be relevant to the consent of participants.

The participant must be informed that his/her personal trial-related data will be used by CNBG and his subsidiaries (Sponsor) in accordance with the local data protection law. The level of disclosure must also be explained to the participant.

The participant must be informed that his/her medical records may be inspected by authorized monitors or Clinical Quality Control personnel appointed by CNBG and its subsidiaries (Sponsor), by appropriate IRB/IEC members, and by inspectors from regulatory authorities.

The Informed Consent Form must also be signed and personally dated by the participant and legal representative or parents/guardian and by the Investigator/person designated by the Investigator to conduct the informed consent discussion. Provision of consent will be confirmed in the eCRF by the Investigator. The signed and dated declaration of informed consent will remain at the Investigator's site and must be safely archived by the Investigator so that the forms can be retrieved at any time for monitoring, auditing and inspection purposes. A copy of the signed and dated information and consent should be provided to the participant prior to participation.

### **11.5. Compensation to Participants**

Appropriate insurance coverage is provided by China National Biotec Group (CNBG) in line with legal requirements and GCP guidance. Details can be consulted at the study site (certificates and conditions in the Investigator Site File). Insurance coverage will be

**CONFIDENTIAL**

---

provided by a local insurance provider.

### **11.6. Participant Confidentiality**

The investigator(s) will respect and protect the confidentiality of the participant in all possible ways. Participant identification, other than participant number, initials and date of birth, will not appear in any Case Report Form (eCRF) pages or other documents given to the Sponsor. Only the investigator and the persons authorized to verify the quality and integrity of the study will have access to participant records where the participant can be identified.

Ensure that the personal privacy of the participants will not be disclosed during the steps of testing, biological sample collection, reporting and publication, etc. Only the participant code, blood sample number, blood collection time and test index are recorded on the package of blood sample. It is strictly limited to the core testing personnel to obtain electronic or written copies.

CONFIDENTIAL

